**xi) Sponsor**

The sponsor of the study will be the London School of Hygiene and Tropical Medicine, [name].

KEMRI, though CMRG-C, Kilifi, will take on the role of database management for active and passive case detection and monitoring of laboratory and field studies. However, SAEs will be reported to the Data Safety Monitoring Board (see below).

**xii) Data Safety Monitoring Board (DSMB)**

An independent committee consisting of experts in malaria, epidemiology, statistics and other appropriate disciplines has been appointed to oversee ethical and safety aspects of the study conduct. A quorum of 3 members is required at scheduled meetings.

The role of the DSMB includes the review of the implementation and progress of the study. It provides initial, regular, and closing advice on safety-related issues to the study sponsor. Its advice is based on the interpretation of study data with reference to the study protocol. The DSMB may, if deemed necessary, convene a meeting with, or request further information from the Principal Investigators and Local Safety Monitors at any stage of the study. The DSMB is empowered to suspend the enrollment to the trial and/or drug treatment on the trial pending review of potential safety issues arising in this trial or other relevant trials of the same drug product. The process will be described in study-specific SOPs. The DSMB will be informed of:

- All SAEs.
- All withdrawals of study subjects by the Principal Investigator or the parent(s)/guardian(s) of a subject due to adverse events.
- New information that may affect adversely the safety of the subjects or the conduct of the study.
- All subsequent protocol amendments, informed consent changes or revisions of other documents originally submitted for review.
- All subsequent protocol modifications (for information).

The final analysis will be conducted by the investigators, but the analysis plan will be discussed with and approved by the DSMB before it is implemented.

### **xiii) Local Safety Monitor (LSM)**

The overall role of the Local Safety Monitors (LSM), who are experienced clinicians based in-country and based in Kilifi or Nairobi, will be to support the clinical investigators and to act as a link between the investigators and the DSMB. The LSM's role will include:

- Acting as the study volunteer's advocate.
- Promptly communicating relevant safety information to the DSMB.
- Providing advice to the investigators on whether a set of clinical circumstances in a study warrants formal notification to the DSMB.
- Conduct a site visit to investigate every report of a SAE
- Unblinding a subject if deemed necessary to allow for adequate treatment.
- Liaising closely with the chair of the DSMB throughout the course of the trial.

The relevant LSM will be informed by the investigator on an 'as received' basis of:

- All SAEs.
- All withdrawals of study subjects by the Principal Investigator or the parent(s)/ guardian(s) of a subject due to adverse events.

### **xiv) Adverse event monitoring**

An adverse event (AE) is defined as "any untoward medical occurrence in a participant or clinical investigation participant administered a pharmaceutical product that does not necessarily have a causal relationship with this treatment" (ICH Guidelines E2A). An adverse event can further be broadly defined as any untoward deviation from baseline health which includes:

- Worsening of conditions present at the onset of the study.
- Deterioration due to the primary disease.
- Intercurrent illness.
- Events related or possibly related to concomitant medications.

A serious adverse event (SAE) is defined as an experience that results in any of the following outcomes:

- Death during the period of study follow-up.
- Life-threatening experience (one that puts a participant at immediate risk of death at the time of the event).
- Inpatient hospitalization during the period of study follow-up.
- Persistent or significant disability or incapacity.
- Specific medical or surgical intervention to prevent one of the other serious outcomes listed in the definition.

#### *Identification of adverse events*

On days 2 and 3 of treatment, study clinicians will assess children according to a standardized clinical record form ([Appendix 8](#)). Children absent from school on these days will be traced at home using information collected from parents during the consenting procedure.

Adverse events will be monitored for a further 28 days using a passive surveillance system in schools and local health centres. Travel costs will be reimbursed and treatment charges waived. Any new event, or an event present at baseline that is increasing in severity, will be considered an adverse event. Adverse events will be monitored until the event has cured or stabilized.

#### *Reporting of adverse events*

For each possible adverse event identified and graded as moderate, severe or life threatening, an adverse event report form will be completed ([Appendix 9](#)). The following information will be recorded for all adverse experiences that are reported:

- Description of event
- Date of event onset
- Date event reported
- Maximum severity of the event
- Maximum suspected relationship of the event to study medication
- Is the event serious?
- Initials of the person reporting the event
- Was the event episodic or intermittent in nature?
- Outcome
- Date event resolved

Grading of events will be based on standard guidelines ([Appendix 10](#)).

#### *Reporting of serious adverse events*

Guidelines for reporting of serious adverse events provided by the KEMRI, the London School of Hygiene & Tropical Medicine, and the data and safety monitoring board (DSMB) will be followed.

#### **xv) Quality control**

All members of the study team will be trained in the study objectives, methods of effective communication with study participants, and collection of high quality data. Study members will receive additional training specific to the tasks they will perform within the study including interviewing techniques, and clinical and laboratory measurements. A random sample of stool, urine and blood samples will be re-read by experienced technicians and any disparities corrected.

### **9. Data management**

#### **Data entry and storage**

All questionnaires will be transferred to Kilifi for review, data entry, and storage. Data will be entered by two independent clerks, will be verified for data entry errors, and corrected from the original questionnaire using customized software (Microsoft Visual FoxPro® 6.0) and verified for accuracy. Study records will be stored securely in KEMRI facilities.

#### **Data analysis**

All analyses will be on the basis of intention-to-treat. To assess the success of randomization baseline characteristics between the four randomization groups will be compared. To assess the impact of the interventions, methods appropriate for cluster-randomized trials will be used (Hayes & Bennett, 1999). The prevalence, or mean, in each school will be calculated and the unadjusted risk ratio (RR), or mean difference (intervention-control), estimated in each stratum. An overall estimate of the effect of IST will be obtained by taking a weighted average of the stratum-specific estimates, the weights proportional to the number of schools per stratum, and 95% confidence intervals will be adjusted for observed between-school variance. Formal hypothesis testing will be undertaken using stratified unpaired t-tests. The impact of each intervention will be estimated for education outcomes and health outcomes in separate multiple regression models. An interaction term will be included to identify any synergistic effects between the two interventions. Statistical analysis will be carried out using STATA® software, version 10.0. (Stata Corporation, Texas, USA).

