#### **4. Background**

Malaria poses an enormous public health burden among the population of Kenya, and several donors are supporting the up-scaling of currently available malaria interventions. Typically, these efforts focus on children under five years and pregnant women because they bear the brunt of morbidity and mortality. However, older children, including those attending school, are also at risk of mortality and morbidity (Lalloo 2006). In addition, malaria greatly contributes to school absenteeism, poor cognition, learning and school performance (Brooker et al., 2000; Holding & Snow, 2001; Lalloo, 2006).

Despite this burden among schoolchildren, there is currently no consensus as to the appropriate approach to malaria control in schools, with relevant intervention strategies likely to vary according to patterns of malaria transmission (Brooker et al., 2008). A promising school-based intervention strategy, already proven effective for improving the health of women in pregnancy, is intermittent preventive treatment (IPT). In a recent study in western Kenya, the mass administration of a full therapeutic course of an anti-malarial drug to schoolchildren once a term, irrespective of infection status, dramatically reduced malaria parasitaemia, almost halved the rates of anaemia, and significantly improved cognitive ability (Clarke et al. 2008; Temperley et al., 2008). The withdrawal in Kenya in 2009 of sulfadoxine-pyrimethamine (SP) and amodiaquine (AQ) from use means that these drugs can no longer be used for IPT. An alternative approach is intermittent screening and treatment (IST), a malaria prevention strategy recently identified in the Kenyan National Malaria Strategy, 2009-2017 as a possible school-based strategy in the newly launched *Malaria Free School Initiative*.

The proposed study will investigate the health and educational impact of school-based IST in a different epidemiological setting in Kenya, where other important contributors to anaemia in school-aged children, including poor nutrition and helminth infections, are important. In addition, the study will investigate a number of scientific and operational issues which yield generate valuable evidence to assist in the formulation of policy recommendations for Kenya and for sub-Saharan Africa.

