**v) Sample size determination**

Power analysis was adjusted for clustering (Hayes & Bennett, 1999) and focused on two main outcomes of interest: the percentage of children who are anaemic (haemoglobin <110 g/L); and education achievement assessed by a battery of tests of reading, writing and arithmetic.

For anaemia, assuming a baseline prevalence of 20% (as found in the 2008 school surveys in Kwale), an intraclass correlation of between 0.025 and 50 children sampled per school, a sample size of 21 schools with a total of 1050 children of all ages in each arm was estimated to provide 80% power to detect a 25% reduction in anemia in the intervention group compared to placebo at 5% level of significance. This equates to 84 schools and 4200 children.

For educational achievement tests, an overall sample size of 100 schools with 50 children per school (5000 children overall) is sufficient to detect an effect size of 0.2 standard deviation (SD) assuming an intra-class correlation of 0.2 (ICC varied from 0.1 to 0.2 with mathematics and literacy tests in Class 2 in 210 schools in Western Kenya; ICC is expected to be lower in Class 1) and a correlation between baseline and final test scores of 0.7. This sample size is sufficient to detect an effect size of 0.15 SD for concentration tests, which have a lower intra-class correlation (0.07 in the previous study in Bondo).

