*Survey procedures:* Seven staff travelling in a single vehicle will visit each school: one supervisor; three laboratory technicians; one laboratory assistant; one nurse; plus one driver. An initial meeting will be held with the head teacher. In order to minimize disruption, one class will be selected at a time. Two education testers will assess cognitive function and educational achievement in the week before the arrival of the health team.

A series of questions will be asked of each randomly selected participating child including: age, fever on the day of the survey, basic household assets indicators, source of potable water in the homestead, use of mosquito nets treated with insecticide (Appendix 3). This information will used to control for potentially confounding variables in the data analysis.

On the day of enrollment to the study, children will have their height measured to the nearest 0.1 cm using a portable fixed base stadiometer and weight measured to the nearest 0.1 kg using an electronic balance.

**No assessment** of malaria parasitaemia and anaemia will be made **at baseline**. However, to measure success of the randomization, children from classes 6 and 7, not enrolled in the study, will be asked to provide a finger-prick blood sample for the preparation of a thick and thin blood smear for malaria investigation. The same finger prick sample will be used at the point of survey to record haemoglobin concentrations using a portable spectrophotometer.

**All enrolled children** in classes 1 to 5 will be asked to provide a finger-prick blood sample at **follow-up** to assess malaria parasitaemia and anaemia.

For those children with a reported fever or a history of fever in the last 48 hours, a drop of blood will be used to perform a rapid malaria test (OptiMal). Any child with a positive test and symptoms will be treated using artemether-lumefantrine (Co-artem) on the day of the survey according to national guidelines or referred to the nearest health facility if necessary. Transportation costs will be provided and an agreement will be reached with facilities to waive appropriate drug costs. Children identified as severely anaemic (haemoglobin levels < 8 g/dL) will receive ferrous sulphate according to national guidelines.

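### The formal test of anaemia takes no child covariates, although baseline predictors are collected; a covariate-adjusted cluster-level test would gain modest precision at no data cost, and the text should say which analysis is primary

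*Protocol*

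**What the plan says.** **Analysis.** Protocol section 9, Data analysis, computes a prevalence or mean per school, with "the unadjusted risk ratio (RR), or mean difference (intervention-control), estimated in each stratum". The stratum estimates are averaged with weights proportional to the number of schools, and formal testing is by stratified unpaired t-tests. The section then adds that health outcomes, as well as education outcomes, will be estimated in multiple regression models. It names no regressor beyond the two interventions and their interaction, and it does not rank the regression against the t-test.

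**Data available.** Under Survey investigations (8 viii), on the day of enrolment "children will have their height measured to the nearest 0.1 cm", and weight is measured too. No analytic use is given for either. The child questionnaire covers age, fever, household assets, water source and net use. The parent questionnaire covers parental education among other items. Both are said to serve control of potential confounders in the analysis. The screening form in section 11 records age and gender.

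**Setting.** The Background describes a setting where "other important contributors to anaemia in school-aged children, including poor nutrition and helminth infections, are important". Haemoglobin and parasitaemia are not measured at baseline in enrolled children; the baseline blood samples come from classes 6 and 7, who are not enrolled. The five randomisation strata (8 vi) are based on past school examination performance.

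**Sample size for anaemia** (8 v). The inputs are a 20% prevalence, "an intraclass correlation of between 0.025 and 50 children sampled per school", and "a sample size of 21 schools with a total of 1050 children of all ages in each arm", for "80% power to detect a 25% reduction in anemia in the intervention group compared to placebo at 5% level of significance". The total is 84 schools; 100 are planned.

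**The concern.** Anaemia is the primary outcome with the least baseline information behind it. It has no baseline value in the cohort and no stratum built on health. It is defined by a single haemoglobin cut-off across standards 1 to 5, so a school's age mix can plausibly shift its prevalence. Age, sex and nutritional status are therefore natural predictors, and they are measured before intervention. A test on raw school prevalences leaves in its error term whatever variation they would explain, together with any chance imbalance in them between the IST and non-IST schools.

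The protocol accepts the principle for its other primary outcome. The sample size for education credits a baseline-to-final correlation of 0.7, and section 8 ix argues that covariates can raise power substantially. Anaemia is credited with nothing.

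There is also an internal mismatch. The survey section assigns questionnaire data to confounder control, but the formal test has no place for covariates. With a regression also planned and no primary analysis named, adjusted and unadjusted anaemia results could both be presented as the main one.

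**Working it through.** **Inputs.** From section 8 v: control prevalence 0.20; 25% relative reduction, so 0.15; 50 children per school; intraclass correlation 0.025 (the text announces a range but prints only this value); 5% significance, assumed two-sided; 80% power. The shares of variance explained by covariates are not in the protocol and are assumed below.

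**Step 1: reproduce the plan's figure.**
- Individually randomised, 0.20 v 0.15: 906 children per side.
- Design effect: 1 + 49 × 0.025 = 2.225.
- 906 × 2.225 = 2,016 children; divided by 50, 40.3 schools; plus one school, 41.3, rounded up to 42 per side.
- 42 v 42 = 84 schools, the stated total, read as the pooled IST v no-IST comparison (21 schools in each of four arms).

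The stated figure is therefore already an unadjusted one.

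**Step 2: unadjusted power.** The variance of a school prevalence is p(1−p) × [0.975/50 + 0.025] = p(1−p) × 0.0445. With c schools per side, SE = √[(0.16 + 0.1275) × 0.0445 / c], and power = Φ(0.05/SE − 1.96).
- c = 42: SE = 0.01745, power 81.7%.
- c = 50 (100 schools): SE = 0.0160, power 87.8%.

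**Step 3: split the variance at p = 0.20.**
- Between schools: B = 0.16 × 0.025 = 0.0040.
- Within schools: W = 0.16 × 0.975/50 = 0.00312.
- Total 0.00712, of which B is 56% and W is 44%.

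**Step 4: effect of adjustment.** If covariates explain a share Rb of B and Rw of W, the SE is multiplied by √{[B(1−Rb) + W(1−Rw)]/(B + W)}. The equivalent number of schools is 100 divided by the variance ratio.

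| Rb | Rw | Variance ratio | SE falls by | Worth, on 100 schools | Power, 50 v 50 |
|---|---|---|---|---|---|
| 0 | 3% | 0.987 | 0.7% | about 1 | 88.2% |
| 10% | 3% | 0.931 | 3.5% | about 7 | 90.0% |
| 20% | 3% | 0.874 | 6.5% | about 14 | 91.7% |
| 40% | 8% | 0.740 | 14% | about 35 | 95.3% |

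**Step 5: within-school variance only.** With Rb = 0 and Rw of 5% or 10%, the variance falls by 2.2% or 4.4%. Power at 50 v 50 moves from 87.8% to 88.5% or 89.2%. Even Rw = 20% gives only 90.5%.

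Any gain worth having must therefore come from the between-school part. Child covariates reach that part only to the extent that schools differ in their mix of age, sex and nutritional status.

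**The case against.** The strongest reply is that the unadjusted analysis is only half the plan. Multiple regression is also announced for health outcomes, and questionnaire data, including age, are committed to confounder control. A covariate list normally belongs in an analysis plan, and section 8 xii refers to one that the DSMB must approve. This stands in part. A reader might infer that anaemia is analysed only unadjusted and that the baseline data go unused; the protocol does not support that, and the unnamed regressors could include height and weight. But the formal test is a stated choice, not a detail deferred. It takes no covariates, and the text does not say whether the regression supersedes it.

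Four further readings go too far:

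- *Height, weight, age and sex are the only child-level predictors.* They are not: net use, fever, assets, water source and parental education are also recorded.
- *The strata do nothing for anaemia.* Section 8 vi says they are meant to capture socio-economic environment as well as school quality, which may relate to nutrition. Some between-school variance may already be removed, and the table makes no allowance for that.
- *The 3% to 37% spread of school anaemia in the 2008 survey is variance waiting to be explained.* It is a range of observed prevalences in 25 schools and includes sampling error. Assuming 50 children per school, the SD is √0.00712 = 0.084, and 25 schools would be expected to span about 33 points.
- *The test is invalid or underpowered.* A stratified cluster-level t-test is valid in a randomised trial, and 84 schools give 81.7% power without adjustment.

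**Conclusion.** The point holds as an inexpensive improvement and a needed clarification; it does not identify an error that threatens the trial. The formal anaemia test uses none of the recorded child covariates, cannot carry out the confounder control promised elsewhere, and is not ranked against the planned regression.

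The standard error would fall by under 1% if covariates explain no between-school variance and only 3% within schools, and by about 3.5% to 6.5% if they explain 10% to 20% between schools. On 100 schools, the latter is worth about 7 to 14 schools. The 14% reduction, worth about 35 schools, needs 40% of the between-school variance explained; nothing in the protocol supports a share that large, so it should not be quoted as the expected gain.

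These figures rest on the printed intraclass correlation of 0.025, 50 children per school, a normal approximation, assumed shares, and no prior gain from the strata.

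**What to change.** In section 9, Data analysis, make the formal test for anaemia a two-stage, covariate-adjusted cluster-level test:

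1. Regress the child's outcome on a pre-specified set of baseline covariates (age, sex, height and weight or z-scores derived from them) and stratum, ignoring arm.
2. For each school, form the ratio of observed to expected anaemia cases, or the mean residual, and apply the stratified t-test already planned to these summaries.

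Keep the unadjusted risk ratio as supporting. State how the multiple regression relates to this test, including whether its role is the interaction term, and which covariates it holds. If questionnaire items such as net use or assets are added, use baseline answers only, since later answers could be affected by the intervention.

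The cost is wording alone: the data are already to be collected, and the sample size does not change. The covariates and the primary analysis should be fixed before any outcome data are seen by arm.

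The stage-one regression adds a modelling step, but the comparison of arms remains at school level, so the cluster-level basis of inference is kept.

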## **8. Design and Methodology**

### **i) General Study design**

This study will be a factorial-design, cluster-randomised, to assess the impact of IST and enhanced literacy instruction by teachers on the health and educational achievement of healthy schoolchildren. This study is one of two studies investigating the health and educational impact of malaria control, with a parallel study planned in Senegal, where malaria transmission is intense but highly seasonal.

The target population in this study includes children attending primary schools in Kenya. The accessible population includes the children attending the participating primary schools in standards 1-7 in Kwale district. The unit of analysis is the school. Schools will be randomized to one of four groups, receiving either the IST intervention alone, the education intervention alone, the IST and education interventions combined, or neither intervention. The first two arms would evaluate the impact of IST. The final two arms would investigate the hypothesis that IST helps children benefit from improved quality of education. Health and educational outcomes will be assessed before intervention and twelve and twenty four months later. The impact of each intervention will be estimated for education outcomes and health outcomes in separate multiple regression models. An interaction term will be included to identify any synergistic effects between the two interventions.

The survey data will be collected over two years – see section 10. Development and testing of survey instruments will take place in 2008. Baseline data collection and intervention activities will commence in January 2009, with follow-up surveys planned in 2010 and 2011. The study will be conducted by the Kenya Medical Research Institute in collaboration with the Division of Malaria Control in the Ministry of Public Health and Sanitation, University of Nairobi, the London School of Hygiene and Tropical Medicine, and Harvard University.

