### **Secondary outcomes:**

3. Prevalence of malaria parasitemia
4. Concentration as assessed by classroom-based tests of sustained attention
5. Classroom behavior as assessed by teacher ratings of children's inattentive and hyperactive-impulsive behaviors.
6. School attendance as assessed by class attendance registers
7. Examination results as assessed by government examination scores

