## **iii) Study sites**

The study will take place in rural primary schools in Kwale district, a hot and relatively dry area on the Kenyan coast. Continuous precipitation supports intense year-round transmission, with two seasonal peaks in malaria cases reflecting the bimodal rainfall pattern, with the heaviest rainfall typically occurring between April and June, with a smaller peak in October and November each year. Most malaria is caused by *Plasmodium falciparum*. A recent survey among 25 schools in 2008 found that the prevalence of malaria infection among schoolchildren in Kwale district was 9% (ranging from 1-28% by school), and 20% (3-37% by school) of children are anaemic ([name], unpublished data). Helminth infections are also common with 38% of schoolchildren estimated to be infected with hookworm and 41% infected with *Schistosoma haematobium*.

Kwale district also has some of the poorest educational indicators in the country, with the district having the worst KCPE examination scores for the last three years running.

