**vi) Randomization and treatment assignment and allocation**

Schools will be randomly assigned to one of the four intervention groups using a pre-defined stratified randomization procedure. A computer generated randomization list will be created by a member of the project who will not be directly involved in the conduct of the study. Sealed copies of the original randomization lists and documentation of the procedure used to generate the lists will be stored in KEMRI offices in Nairobi. Prior to the onset of the study, sealed copies of the randomization lists will be distributed to the member of the study team responsible for treatment allocation.

Schools will be stratified into five groups according to school examination performance in previous years, to account for differences in school quality and socio-economic environment. Five schools will be randomly selected from each school-performance stratum, and within each stratum schools were randomly allocated to 1 of 5 coded drug groups using block randomization according to the randomization listing.

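### Read literally, the plan averages stratum risk ratios on the ratio scale, which biases the pooled ratio upward: about 6-8% for parasitaemia in the IST main effect, about 2% for anaemia

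*Protocol*

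**What the plan says.** Protocol section 9, Data analysis, sets the estimator out in two steps. First: "The prevalence, or mean, in each school will be calculated and the unadjusted risk ratio (RR), or mean difference (intervention-control), estimated in each stratum". Second, the overall IST effect comes from "taking a weighted average of the stratum-specific estimates", with "the weights proportional to the number of schools per stratum". The confidence interval is adjusted for between-school variance, and testing is by stratified unpaired t-tests. Regression models with an interaction term are also planned. No log transformation is mentioned.

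The strata are defined in section 8.vi: "Schools will be stratified into five groups according to school examination performance in previous years". Section 8.i says "Schools will be randomized to one of four groups", in a factorial layout. Section 8.v plans 100 schools with 50 children each.

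The outcome most exposed is the secondary outcome "Prevalence of malaria parasitemia". Section 8.iii reports from 25 schools surveyed in 2008 that malaria infection "in Kwale district was 9% (ranging from 1-28% by school"), and that anaemia was 20% (3-37% by school).

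**The concern.** Each stratum risk ratio has an estimated control prevalence as its denominator. By Jensen's inequality the expected ratio exceeds the true ratio, to second order by the squared coefficient of variation of that control mean. Averaging five such ratios reduces their variance but leaves the bias in place. Widening the confidence interval for between-school variance does not move the point estimate.

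The bias matters most where prevalence is low and schools differ widely, which describes parasitaemia. IST acts on that outcome directly, and reducing it is specific objective 2. For an effective intervention the reported effect is pulled towards no effect. The point estimate can also sit slightly out of line with the t-test on the same school prevalences.

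**Working it through.** **The plan's own figure.** The protocol gives no figure for this bias. Its anaemia sample size (section 8.v) does show which comparison the design supports. For 20% v 15% at 80% power and two-sided 5%, 906 children per side are needed without clustering. The design effect is 1 + 49 × 0.025 = 2.225. Then 906 × 2.225 / 50 = 40.3, plus one school = 41.3, rounded up to 42 schools per side. That is two cells of 21, or 84 schools, as stated. Power is 81.6% for 42 v 42 schools and 52% for 21 v 21. The stated number therefore fits the factorial margin: all IST schools against all non-IST schools.

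**Inputs**
- Five strata (section 8.vi); 100 schools and 50 children per school (section 8.v).
- Assumption: equal strata of 20 schools, so m = 10 control schools per stratum for the margin and m = 5 for a single-arm comparison.
- Parasitaemia: p = 0.09, range 0.01-0.28 over 25 schools (section 8.iii). Observed SD ≈ 0.27 / 3.93 = 0.069, where 3.93 is the expected range of 25 normal values in SD units. Binomial variance is then removed for an assumed 50 or 100 children surveyed per school:
  - √(0.0687² − 0.09 × 0.91/50) = 0.056
  - √(0.0687² − 0.09 × 0.91/100) = 0.062
- Anaemia: p = 0.20, ICC 0.025, so SD = √(0.025 × 0.20 × 0.80) = 0.063.

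**Second-order approximation.** Relative bias ≈ (CV² + (1 − p)/(50p)) / m, where CV = SD/p.
- Parasitaemia, m = 10, SD 0.056: (0.387 + 0.202)/10 = 5.9%.
- Parasitaemia, m = 10, SD 0.062: (0.475 + 0.202)/10 = 6.8%.
- Parasitaemia, m = 10, half of the between-school variance absorbed by the strata: (0.194 + 0.202)/10 = 4.0% to (0.237 + 0.202)/10 = 4.4%.
- Anaemia, m = 10: (0.100 + 0.080)/10 = 1.8%, so 0.75 becomes 0.75 × 1.018 = 0.764.

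**Simulation.** 20,000 trials with beta-distributed school prevalences capture the higher-order terms. Parasitaemia ranges run over SD 0.056-0.062.

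| Outcome | Schools per stratum | True RR | Mean of stratum RRs | Log-scale mean |
|---|---|---|---|---|
| Parasitaemia | 10 v 10 | 1.00 | 1.06-1.08 | 1.01 |
| Parasitaemia | 10 v 10 | 0.75 | 0.80-0.81 | 0.76 |
| Parasitaemia | 5 v 5 | 1.00 | 1.14-1.18 | 1.03-1.04 |
| Parasitaemia | 5 v 5 | 0.75 | 0.86-0.88 | 0.77 |
| Anaemia | 10 v 10 | 0.75 | 0.764 | 0.75 |
| Anaemia | 5 v 5 | 0.75 | 0.778 | 0.75 |

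At a true RR of 0.75 (10 v 10) the planned estimator has an SD of about 0.14, so a bias of 0.05 is 0.05/0.14 ≈ 0.36 of a standard error. At a true RR of 1.00 (10 v 10), about 62% of trials give an estimate above 1.

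The log-scale estimator is also the more precise: at a true RR of 1.00 (10 v 10) its SD is about 0.16-0.17, against 0.17-0.19 as planned.

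With logit-normal school prevalences and strata that absorb half of the between-school variance, the 10 v 10 parasitaemia bias was 4.5-5.0% for SD 0.056-0.060, and 6.0% for SD 0.069.

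**The case against.** **The protocol never says that the average is arithmetic.** One clause covers both risk ratios and mean differences, and averaging logs would be compatible with it. A separate analysis plan, to be approved by the DSMB, may fix the scale. This stands as a limit, and the point is conditional on the literal reading. But the protocol does specify the estimator (ratio, pooling rule and weights), so this is a poorly fixed choice and not just a detail left for later.

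**The consequences are modest.** Parasitaemia is secondary, the bias for anaemia is negligible, the formal test is a t-test that is not distorted in this way, and regression models are also planned. All of this stands.

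**The inputs are soft.** The SD comes from a minimum and maximum over 25 schools, with an assumed number surveyed per school. This also stands, and is why a range is given.

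**Three stronger readings are tempting but not supported.**
- A reader might take 14-18% as the bias. That needs single arms compared, 5 v 5. Section 8.i does say that the first two arms evaluate IST, but the first two it lists are IST alone and education alone, which is not an IST-versus-control contrast. The sample size fits the margin.
- A reader might infer that the estimate is pushed past no effect. For an effective IST it is not: 0.75 becomes about 0.80. Only at a true null does the average lie above 1, by less than half of a standard error.
- A reader might apply the statement "Five schools will be randomly selected from each school-performance stratum" and find a far larger bias. That sentence conflicts with 100 schools and four arms elsewhere in the protocol. It needs reconciling and cannot serve as the basis for the size of this bias.

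**Conclusion.** The concern holds in a limited form. On the literal reading, the pooled risk ratio for parasitaemia is too high by about 6-8% for the IST main effect, or about 4-6% if the strata take up half of the between-school variance. A true 25% reduction would be reported on average as about 20%. For the primary outcome anaemia the bias is about 2%.

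The figures rest on five equal strata of 20 schools, 50 children per school and an inferred between-school SD of 0.056-0.062. The bias is systematic and avoidable, but it is about a third of a standard error on a secondary outcome and leaves the hypothesis test alone. Severity: minor to moderate.

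**What to change.** In section 9, Data analysis, state that for binary outcomes the log risk ratios are averaged across strata with the same school-number weights and back-transformed, with the confidence interval calculated on the log scale. In the 10 v 10 setting this cuts the parasitaemia bias to about 1-1.5% and slightly improves precision.

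The cost is one sentence plus a fallback rule, because a log risk ratio is undefined when a stratum arm has no cases. That is rare at 10 v 10. A suitable fallback is the ratio of the stratum-weighted mean prevalences, which showed a similarly small bias (about 0.76 for a true 0.75). It targets a slightly different quantity if the risk ratio varies by stratum, so the text should say when it applies.
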